## **PROJECT PROPOSAL**

### ***Background***

The efficacy of social marketing campaigns in facilitating a societal shift in beliefs and attitudes towards low back pain (LBP) is well established. Evidence suggests that campaigns need to be exhaustive and utilise multimedia. The Spinal Pain Model of Care recommends the use of social marketing strategies in WA, specifically mass media campaigns. Development of a single, Government-issued resource which delivers simple, evidence-based messages to the public about active pain management strategies for LBP is the first step in developing a suite of social marketing resources for minimising the burden of spinal pain in WA.

The Spinal Pain Implementation Working Group (SPIWG) has developed a consumer pamphlet which contains evidence-based information about the course of, and self management strategies for, acute and chronic LBP. The pamphlet will be aimed at individuals who seek care for, or information about, LBP in primary care settings (eg pharmacies, GP practices, allied health practices).

The pamphlet has undergone a period of consultation with key professional health bodies and health stakeholders. The pamphlet content is supported by the following professional bodies: Australian Clinical Psychology Association; Australian and New Zealand College of Anaesthetists; Australian Osteopathic Association; Australian Pain Society; Australian Physiotherapy Association; Australian Rheumatology Association (WA); Chiropractors' Association of Australia; Health Consumers' Council; Pharmaceutical Society of Australia (WA); and the Royal Australian College of General Practitioners. Providing the opportunity for the professional bodies of different disciplines to endorse the pamphlet content encourages inter-professional consistency in the delivery of evidence-based information to individuals who seek information about spinal pain. Additionally, messages are targeted towards best-practice *self-management* of spinal pain, where appropriate. Where additional support is required, recommendations to seek evidence-based guidance by health professionals are encouraged.

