## ***Design***

A randomized, controlled trial, consisting of 3 study arms (A, B and C), will be undertaken in partnership with 20 community pharmacies in the Perth metropolitan area. A convenience sample of pharmacies will be selected through the PSA-WA. Participating pharmacies will cover major zones of the Perth metropolitan area to represent a range of socioeconomic levels. Ten pharmacies will be involved in both the 'control' (A) and 'pamphlet only' (B) arms while a separate ten pharmacies will be involved in the 'pamphlet with education' (C) arm only. Pharmacies will be allocated to study groups randomly. Each pharmacist who participates in the workshop, will receive training from the evaluation team according to their allocated study arm and remuneration for recruitment.

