## ***Participants***

Pharmacists and/or pharmacy staff will identify individuals who present to the pharmacy to purchase pain-relieving medications for LBP by:

- i) asking customers about the reason for their medication purchase or GP medicine prescription;
- ii) answering questions from customers about medication options for LBP or;
- iii) customers approaching pharmacy staff about the study in response to posters placed in the pharmacy which advertise the study.

Any pharmacy customer aged 18-70 years who is currently experiencing low back pain and has adequate understanding of written and spoken English is eligible to participate. There are no exclusion criteria for this study. Each pharmacy will recruit 12 consecutive customers who meet the inclusion criteria for each study arm. The total sample size will therefore be N=360. Customers who are interested in participating will be asked to complete a consent form and a baseline questionnaire. The completed form and questionnaire will be sent by the pharmacy to Curtin University in a reply paid envelope.

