### ***Outcome measures***

Data will be collected at baseline (T0) and then at 2 weeks (T1), and 8 weeks (T2) after the intervention. Table 1 shows which outcomes measures will be measured at particular time points. Beliefs about back pain will be collected using the Back Pain Beliefs Questionnaire and fear avoidance behaviours will be collected using the Fear Avoidance Beliefs Questionnaire. Pain intensity and disability will be measured using an 11 point numeric rating scale (NRS). Demographic (age, gender, highest level of education) and pain history characteristics (duration of symptoms) will be measured at baseline only while an 11 point NRS for Global Perceived Impression of Usefulness will be used at time points subsequent to baseline to measure the usefulness of the pamphlet.

**Table 1:** Outcome measures assessed by time point.

| Instrument | T0 | T1 | T2 |
|-------------------|-----------|-----------|-----------|
| Demographics      | ✓         |           |           |
| Pain history      | ✓         |           |           |
| BPBQ              | ✓         | ✓         | ✓         |
| FABQ              | ✓         | ✓         | ✓         |
| Pain intensity    | ✓         | ✓         | ✓         |
| GPIU              |           | ✓         | ✓         |
| Disability        | ✓         | ✓         | ✓         |

Participants will be asked to provide informed consent at baseline, including their contact details and date of birth. All data will be collected using a 2 page, teleform paper questionnaire which will be de-identified but linked to person details using a unique study identifier. Data at T0 will be collected onsite at the pharmacy while follow-up questionnaires (T1, T2) will be posted to participants with a reply-paid envelope. All data will be returned to Curtin University for secure storage and analysis. Participants who do not return follow-up questionnaires will be contacted by a project officer and reminded to do so.

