### ***Interventions***

Interventions will be phased in the following sequence:

**A) Control (pharmacies 1-10):** pharmacists will be asked to invite the first 12 customers who meet the inclusion criteria to participate in the study as a control (N=120). In the control arm, customers will not receive any information about self-management for LBP (i.e.; will receive ‘usual care’ only).

**B) Pamphlet only (pharmacies 1-10):** pharmacists will be asked to invite the next 12 customers, that is the next 12 customers after the control participants have been recruited, who meet the inclusion criteria, to participate in the study (N=120). In this arm, participants will receive a pamphlet from the pharmacist without any further information about self management, other than usual instructions from the pharmacist relating to medication intake, dosage and side-effects. Baseline data will be collected *prior to* the pamphlet being provided.

**C) Pamphlet with education (pharmacies 11-20):** pharmacists will be asked to invite the first 12 customers who meet the inclusion criteria to participate in the study (N=120). In this arm, participants will receive a pamphlet from the pharmacist *and* the pharmacist will review the content of the pamphlet with the participant. Information provided by pharmacists will be standardised. Baseline data will be collected *prior to* the pamphlet and further information being provided. The role of the pharmacist will be to reinforce the key messages contained in the pamphlet

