### ***Analysis***

A 3x3 ANOVA with one repeated measure will be used to examine main effects for group (k=3) and time point (k=3), as well as interactions between the factors.

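### The planned group-by-time ANOVA leaves out symptom duration and baseline pain, although the arms are not individually randomised and an imbalance in either could bias the contrasts

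*Supplement*

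**What the plan says.** Eligibility (Participants) is open as to duration: "Any pharmacy customer aged 18-70 years who is currently experiencing low back pain" may join if their English is adequate, and "There are no exclusion criteria for this study". The mixed population is deliberate, since the Background describes the pamphlet as giving "information about the course of, and self management strategies for, acute and chronic LBP".

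The Design section states that "Pharmacies will be allocated to study groups randomly". Customers are not randomised. In pharmacies 1-10 the first 12 eligible customers are controls, and arm B is formed from the following ones, "that is the next 12 customers after the control participants have been recruited" (Interventions). For the third arm, "a separate ten pharmacies will be involved in the 'pamphlet with education' (C) arm only".

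Under Outcome measures, "pain history characteristics (duration of symptoms) will be measured at baseline only", and Table 1 schedules pain intensity at T0, T1 and T2. The analysis is one sentence: "A 3x3 ANOVA with one repeated measure will be used to examine main effects for group (k=3) and time point (k=3", plus the interaction. It contains no covariate, stratum or pharmacy term.

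**The concern.** The A-B comparison has no randomisation, and the comparisons with C rest on ten pharmacies a side. Nothing at customer level makes the arms alike in how long people have had pain or how severe it is.

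If people with recent pain and people with long-standing pain change by different amounts over eight weeks, a different mix between arms shows up as a group-by-time effect. A model with only group and time cannot separate that from an effect of the pamphlet. At stake are the size of the estimated effect, the false-positive rate and some precision, all of which could be improved with data the trial already collects.

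**Working it through.** **The plan's own figures.** Appendix 1 uses SD 5.0, 80% power and alpha 0.05, with differences of 1.9 points (BBQ) and 1.5 points (FABQ-phys). A two-sided two-sample t-test gives 109.7 and 175.4 per group, rounded up to 110 and 176, as stated. At the planned 120 per arm, power by the normal approximation is 83.7% and 64.2%. The point here concerns the model, not these figures.

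**Mechanism.** A simulation used 4,000 runs, 120 per arm, one baseline and one follow-up visit, outcome SD 5.0 and r = 0.5. The chronic share was set at 40% against 60%, a deliberately large gap. There was no true arm effect, and chronic participants scored 3 points lower at baseline.

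| Acute-chronic difference | Bias, unadjusted | Type I error | Type I error with duration in the model |
|---|---|---|---|
| Same level gap at both visits | 0.00 | 4.9% | 4.9% |
| Chronic also change 2 points less | -0.41 | 9.0% | 5.0% |
| Chronic also change 3 points less | -0.60 | 13.8% | 5.1% |

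A stable difference cancels in the group-by-time contrast. Bias appears only when duration predicts change, and adjusting for duration removes it (residual within 0.01 points).

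**Plausible imbalance.** Assume 50% chronic. The chance SD of the difference in share between two arms of 120 is √(2 × 0.5 × 0.5 / 120) = 0.065, so the 95% range is about ±13 percentage points. With an assumed ICC of 0.10 the variance is multiplied by 1 + 11 × 0.10 = 2.1, and the range is about ±18 points. The wider range is relevant to C, because A and B share pharmacies.

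**Bias.** Bias = (difference in chronic share) × (acute-chronic difference in mean change), both assumed:
- Low: 0.10 × 1 = 0.1 points, which is 5% of 1.9 and 7% of 1.5.
- High: 0.13 × 3 = 0.39, about 0.4 points, which is 21% of 1.9 and 26% of 1.5.

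With SE = 5 × √(2/120) = 0.645, a fixed bias of 0.1 gives a type I error of 5.3%, and 0.4 gives 9.5%.

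**Precision from the baseline outcome.** With r the correlation between baseline and follow-up, the variance of change is proportional to 2(1 - r) and that of the baseline-adjusted score to 1 - r². The reduction is (1 - r)/2. BBQ power is for 1.9 points, 120 per arm, no clustering and full follow-up.

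| Assumed r | Variance cut | BBQ power, change → adjusted |
|---|---|---|
| 0.3 | 35% | 70% → 87% |
| 0.5 | 25% | 83% → 92% |
| 0.7 | 15% | 97% → 98% |

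**Precision from duration and baseline pain.** With residual SD 5 × √(1 - R²) and assumed R² of 0.02, 0.05 and 0.10, BBQ power at 120 per arm goes from 83.7% to 84.5%, 85.5% and 87.3%. FABQ-phys power goes from 64.2% to 65.1%, 66.4% and 68.8%.

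**The case against.** The best defence is that T0 is one level of the time factor, so the interaction already removes stable differences between arms. That is correct, and it confines the problem to differential change. It does not protect the group main effect, which the plan also intends to examine and which averages T0 in.

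Second, A and B draw consecutive customers from the same pharmacies, and C is set by random allocation of pharmacies, so case mix may be close. For C, imbalance in pharmacy case mix is a matter of chance, and the bias above is conditional on the imbalance that occurs. For A against B there is no randomisation to appeal to.

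Third, pooling acute and chronic pain is the intended pragmatic population, and covariates are often left to an analysis plan, which is not shown. Pooling is indeed no fault. But the protocol does name its model, and that model uses none of the baseline covariates collected.

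Fourth, baseline adjustment is not free when arms are non-equivalent. A persistent baseline gap of D leaves about (1 - r)D in the adjusted contrast but cancels in change. With assumed D = 1 and r = 0.5 that is 0.5 points, more than the bias being removed. This objection stands, and the fix has to allow for it.

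Two stronger readings are tempting. A reader might infer a bias of up to 0.6 points, or 32% of the BBQ target. That needs a 20-point imbalance, beyond the chance range of about 13-18 points, together with a 3-point difference in change. Nothing in the documents indicates either. A reader might also credit duration and baseline pain with raising power from 83% to 92%. That gain comes only from using the baseline outcome as a covariate instead of change, at r = 0.5 and ignoring clustering. The documents give no r.

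**Conclusion.** The point holds as a conditional weakness of the stated analysis. The arms lack individual randomisation, duration and pain are measured at T0, and the model uses neither as a covariate. If either predicts change in beliefs or fear avoidance, a chance or selection imbalance biases the group-by-time contrast by roughly 0.1-0.4 points, under the assumed 10-13 point imbalance and 1-3 point difference in change. The documents establish neither input, so they do not show that the trial will be biased, only that the plan leaves this route open. The gain in precision is a secondary benefit: it depends on r, and duration and baseline pain contribute modestly to it.

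**What to change.** Replace the ANOVA sentence with a linear mixed model of the T1 and T2 scores. Fixed terms are arm, time, arm-by-time, the baseline value of the outcome, symptom duration as recorded and baseline pain intensity (entered once when pain is itself the outcome). Pharmacy and participant are random effects. Base conclusions on the adjusted arm contrasts. Enter duration as recorded, because the available text defines no acute/chronic cut-off.

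Prespecify, as a sensitivity analysis, the change-from-baseline contrast adjusted for duration and baseline pain. With non-equivalent arms the two analyses can differ, and a material difference should be reported and discussed.

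State that the adjustment covers only measured covariates. Calendar-time effects and recruiter selection in the A-then-B sequence remain.

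The cost is a change of wording, a slightly more complex analysis and one sensitivity analysis. No new data are needed.

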## ***Aim***

The aim of this project is to undertake an evaluation of the LBP pamphlet within a primary care context. The SPIWG will partner with Curtin University and the Pharmaceutical Society of Australia (WA) (PSA-WA) for the evaluation. The project will determine whether providing the pamphlet to individuals who visit a community pharmacy to purchase pain-relieving medications for LBP is effective in improving beliefs about LBP and minimising fear avoidance behaviours related to LBP, compared to not providing the pamphlet. A secondary aim is to determine whether providing the pamphlet with the pharmacist reiterating the key messages to the consumer is more effective than providing the pamphlet alone.

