**Total**

**\$14,300**

***Appendix 1: Sample size estimates***

BBQ: assuming a mean change of 1.9 points (based on population response in Victoria from Buchbinder et al 2001), STDEV 5.0 (based on WA survey) and 80% power and alpha 0.05, sample of 110 per group needed (N=330).

FABQ-phys: assuming a mean change of 1.5 points (based on population response in Victoria from Buchbinder et al 2001), STDEV 5.0 (based on WA survey) and 80% power and alpha 0.05, sample of 176 per group needed (N=528).

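### The 3x3 ANOVA counts the pre-intervention score as an outcome level and names only omnibus tests, so its group main effect is not the intervention effect and no planned test isolates either aim

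*Supplement*

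**What the plan says.** The Analysis section is one sentence. It specifies a 3x3 ANOVA with one repeated measure, to "examine main effects for group (k=3) and time point (k=3), as well as interactions between the factors". It names no contrast, baseline covariate or principal time point, and does not say which effect answers which aim.

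The Outcome measures section fixes the three time levels: "Data will be collected at baseline (T0) and then at 2 weeks (T1), and 8 weeks (T2) after the intervention". Table 1 schedules both belief questionnaires at all three. Under Interventions, arm B is described thus: "Baseline data will be collected *prior to* the pamphlet being provided". Arm C has an equivalent statement, and arm A receives no pamphlet.

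The Aim section poses two specific comparisons. The first is whether giving the pamphlet "is effective in improving beliefs about LBP and minimising fear avoidance behaviours related to LBP, compared to not providing the pamphlet". The second is whether "providing the pamphlet with the pharmacist reiterating the key messages to the consumer is more effective than providing the pamphlet alone".

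**The concern.** No intervention effect can exist at T0. A group main effect that averages over T0, T1 and T2 mixes one time point without an effect with two that may have one. It also absorbs any baseline difference between arms. Such differences are plausible here: A and B are recruited one after the other in the same ten pharmacies, and C comes from ten others. The time main effect, averaged over arms, includes natural recovery and is not an intervention effect.

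That leaves the interaction, which compares change over time across all three arms at once. A significant result says that the arms did not change alike. It does not say whether the pamphlet beat no pamphlet, or whether education added anything. The trial could report a significant F-test with both questions unanswered, or a reader could take the diluted group effect as the size of benefit.

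**Working it through.** **Inputs from the documents.** 120 per arm (Interventions). Planning effects of 1.9 (back beliefs) and 1.5 (FABQ-phys), SD 5.0, 80% power, alpha 0.05 (Appendix 1).

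**Assumptions.** Two-sided tests. The planning effect is taken as the between-arm difference at both T1 and T2, with no expected difference at T0. The correlation r between any two time points is equal; the documents give no value, so 0.3 to 0.7 is shown. Clustering by pharmacy and dropout are ignored.

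**1. The plan's own figures.** A two-sample t-test with these inputs needs 109.7 per group for 1.9 and 175.4 for 1.5. Rounded up, these are the stated 110 and 176. The inputs are therefore read correctly for a two-group comparison.

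**2. Group main effect.** With effects d1 at T1 and d2 at T2 it estimates (0 + d1 + d2)/3, which is two thirds of their mean.
- 1.9: (0 + 1.9 + 1.9)/3 = 1.27
- 1.5: (0 + 1.5 + 1.5)/3 = 1.00

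The variance of a person's three-time mean is 25(1 + 2r)/3. If B and C both differ from A by 1.9, the noncentrality is 120 × 1.27² × (2/3) / [25(1 + 2r)/3], using the unrounded 1.267. At r = 0.5 this is 7.70 on 2 and 357 df.

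**3. Interaction.** Its noncentrality is 120 × S / [25(1 − r)], where S is the sum of squared interaction terms. S factors into d² × (sum of squared centred arm pattern) × (sum of squared centred time pattern).
- Time pattern (0, 1, 1), centred (−2/3, 1/3, 1/3): sum of squares 6/9.
- B and C both improve, arm pattern (0, 1, 1): sum of squares 6/9.
- Only C improves, arm pattern (0, 0, 1), centred (−1/3, −1/3, 2/3): sum of squares 6/9.

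S is 1.9² × 4/9 = 1.604 in both cases. At r = 0.5 the noncentrality is 120 × 1.604/12.5 = 15.40 on 4 and 714 df. The two patterns give the same power, although they give opposite answers on whether the pamphlet alone works and whether education adds to it.

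**4. Pairwise contrast at T2.** The SD is 5√(1 − r²) with baseline as a covariate and 5√(2(1 − r)) for change from baseline. At r = 0.5 these are 4.33 and 5.00. Power is from the two-sample t-test with 120 per arm.

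Results for 1.9 points:

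| r (assumed) | Group main effect, 2 df | Interaction, 4 df | T2 contrast, baseline as covariate | T2 contrast, change score |
|---|---|---|---|---|
| 0.3 | 80% | 76% | 87% | 70% |
| 0.5 | 70% | 90% | 92% | 83% |
| 0.6 | 65% | 96% | 96% | 91% |
| 0.7 | 61% | 99% | 98% | 97% |

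For 1.5 points, at r = 0.3/0.5/0.6/0.7:
- Group main effect: 58%/48%/45%/41%
- Interaction: 53%/69%/80%/91%
- Baseline-adjusted T2 contrast: 68%/76%/82%/90%

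**The case against.** The strongest reply is that the sentence also lists the interaction, "as well as interactions between the factors", which is the conventional test of an intervention in a baseline-plus-follow-up ANOVA. It is not diluted by T0, and its error term is within-person, so the baseline scores do buy precision. This stands. A reader might infer that the plan is likely to miss a real effect, or that it wastes the baseline data. The documents support neither. For 1.9 points the interaction has 90% power or more from r = 0.5 upward, much the same as the adjusted pairwise contrast. Setting the weak group main effect against that contrast would not be a like-for-like comparison. The fair comparator for a directed test is the change-score contrast, over which the gain is 17 percentage points at r = 0.3 and about 2 at r = 0.7.

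A second reply is that this is a project proposal with no separate analysis plan shown, and that follow-up contrasts and testing order are commonly left to such a plan. This stands in part: their absence alone would not be a finding. What can be faulted is the model that is stated, in which T0 is an outcome level and the group main effect is to be examined.

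A reader might also infer that Appendix 1 sizes a comparison the trial will never make. That goes too far. The appendix names no test and speaks only of a mean change ("BBQ: assuming a mean change of 1.9 points"). The two-sample reading comes from reproducing its figures and may equally suggest that pairwise comparisons were intended.

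**Conclusion.** The point holds in this limited form. The group main effect of the stated ANOVA estimates two thirds of the mean follow-up effect, plus one third of any baseline difference, and should not be read as the intervention effect. The two-thirds figure is exact whenever the expected T0 difference is zero. The interaction can detect that arms changed differently, and does so well for 1.9 points at moderate to high correlation, but it cannot tell the two aims apart.

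The power figures rest on an assumed correlation, equal effects at T1 and T2, no dropout and no clustering. They fit C minus B least well, because that comparison is between different pharmacies. Baseline adjustment reduces the influence of measured baseline differences. It does not turn consecutive cohorts, or customers of different pharmacies, into individually randomised groups.

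**What to change.** Replace the Analysis sentence with a model of the T1 and T2 scores that has the baseline score as a covariate and terms for arm, time and arm-by-time. Name one follow-up time and pre-specify two contrasts there:
- Pamphlet versus no pamphlet, for the main aim. B minus A is the form that compares arms within the same pharmacies. If B and C are to be pooled instead, say so.
- C minus B, for the secondary aim.

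State that the group and time main effects of a three-time ANOVA will not be interpreted as intervention effects. Do not use a model that forces equal baseline means across arms: A and B are consecutive cohorts and C comes from other pharmacies, so the design does not guarantee that equality.

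The cost is analysis wording only. Both belief questionnaires are already scheduled at T0, T1 and T2, so no visit, item or participant is added.
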